## Abstract

**Introduction:**

Young people in out-of-home care have often experienced trauma, such as direct maltreatment or witnessing violence. There is good evidence that rates of mental health difficulties are high in this group, including posttraumatic stress disorder (PTSD), a trauma-specific mental health outcome. There remains less evidence to guide how to effectively address elevated PTSD symptoms (PTSS) in these young people, particularly in ways that are feasible and scalable for stretched social-care and mental health services.

**Methods and analysis:**

This protocol describes a feasibility study comprising a pilot two-arm randomised controlled trial (RCT). Participants (*N* = 50) will be randomised to either (a) a group-based trauma-focused programme (Teaching Recovery Techniques), delivered by mental health practitioners both online and in-person, or (b) care-as-usual. Primarily, the trial aims to explore the key feasibility and protocol acceptability questions, including rates of recruitment and retention, as well as the acceptability of the intervention (particularly the online delivery format) to participants and services. In addition, outcomes including PTSS (primary clinical outcome), depression and functioning will be assessed at baseline (pre-randomisation), post-intervention and at a 3-month follow-up.

**Ethics and dissemination:**

Ethical approval has been received from the Health Research Authority (Wales REC1 Ref 20/WA/0100) and University, with further approval from the host trust and social care site. The results will inform the design of a definitive RCT. Dissemination will include peer-reviewed journal articles reporting the qualitative and quantitative results, as well as presentations at conferences and lay summaries.

**Trial registration:**

ClinicalTrials.gov, NCT04467320. Registered on 13 July 2020.

In the UK, there are currently over 90,000 young people under the care of local authorities [11]. Most commonly, these young people have been exposed to significant abuse and/or neglect in their family homes. Most are also removed from school-age or older, meaning many of these experiences have potentially been prolonged [11]. Once in care, many face continued instability and uncertainly, including regular changes in placement providers and separation from siblings (e.g. [17, 22, 25]). Whilst some young people in care can be very resilient to these difficult experiences, it is also the case that high rates of mental health difficulties are commonplace. In the UK, young people in care are five times more likely to meet the criteria for a psychiatric disorder compared to their peers [14], and the trajectory of these difficulties is commonly chronic and enduring [17, 30]. Failing to adequately address the mental health needs of this group has been identified as a key driver of lifelong difficulties, including the higher rates of homelessness, unemployment and contact with the prison system (e.g. [18]).

Whilst young people in care are at risk of developing a range of potential mental health difficulties, one such outcome is posttraumatic stress disorder (PTSD)—a trauma-specific mental health difficulty [1]. Rates of PTSD are up to 12 times higher in young people in care, compared to their peers [14]. In the 5th edition of the Diagnostic and Statistical Manual of Mental Disorders (DSM-5), PTSD is categorised by four core symptom clusters: re-experiencing (e.g. intrusive memories, nightmares), avoidance (e.g. thought suppression, avoiding reminders of the trauma), negative alterations in mood and cognition (e.g. shame, fear, feeling detached), and altered arousal (e.g. problems sleeping, aggression) [1]. If left unaddressed, PTSD can become chronic, with enduring effects on well-being across the lifespan [20].

The current first-line recommended treatment for PTSD, including for children and teens exposed to maltreatment, is a manualised trauma-focused cognitive behavioural therapy (tf-CBT) [23]. Tf-CBTs are generally delivered in a 1:1 format as 8–20 sessions, with closer to 20 sessions recommended for more complex presentations, such as those that might often be expected for young people in care. There is good evidence that tf-CBTs are an effective treatment for maltreated young people, including in more complex cases (e.g. [7, 10, 21, 23, 26]). However, given the large number of young people in care potentially struggling with elevated PTSD symptoms (PTSS), and the well-documented capacity problems in child and adolescent mental health services (CAMHS), higher-intensity treatments alone are not a feasible avenue for addressing the problem [9]. Whilst some young people in care with very complex presentations will certainly require high-intensity psychological support, developing more easily scalable and feasible lower-intensity interventions may be one way to target the needs of a larger group of young people.

One such potential lower-intensity intervention is Teaching Recovery Techniques (TRT), developed by the Children and War Foundation [34]. TRT is a CBT-based seven session group programme for young people with elevated PTSS, with five sessions for the young person and two additional sessions for the caregiver. Sessions target key maintainers of elevated PTSS [16, 32], particularly around psychoeducation, coping strategies and memory qualities. There is growing evidence that TRT is a potentially effective intervention for reducing PTSS in young people exposed to war traumas [4, 5]. There is also some preliminary evidence that it may reduce subjective distress in a small sample of young people living in secure accommodation in the UK [6].

## Aims

The primary goal of this study is to determine the feasibility both of delivering TRT as a lower-intensity online or in-person intervention and of recruiting, retaining, and collecting outcome data on young people in care with elevated PTSS. The results of this study will be used to inform a larger definitive trial. The specific aims are as follows:Investigate core procedural and protocol uncertainties for a later-stage definitive trial, including (a) engagement of social workers in routine screening for PTSS using a validated screening tool (see the ‘Measures’ section); (b) uptake of the intervention by young people and carers, including the proportion who are eligible and who agree to randomisation, and retention rates; (c) intervention facilitator engagement in training, adherence to the manual and capacity to monitor fidelity; (d) selection of secondary outcome measures; (e) outcome measure metrics and variances to estimate the sample size required for the full trial; and (f) the appropriateness of trial procedures, including inclusion/exclusion criteria and using care-as-usual for the comparison condition.Explore the acceptability of the intervention and key practical considerations from the perspective of stakeholders, including (a) young peoples’ experiences of the programme components, including the group and online delivery format; (b) carers’ experiences of supporting young people through this programme and their own engagement in carer sessions; (c) engagement in assessments (e.g. rates of assessment completion); (d) engagement of young people who may not have a consistent caregiver; (e) the appropriateness of mixed-gender groups and groups where young people may have varied maltreatment experiences; and (f) whether the manual needs further refining before any future trial.

## Methods

### Trial design

This trial will comprise a two-arm feasibility RCT, in which participants will be randomly assigned to either the online TRT intervention or care-as-usual (CAU). Participants will be assessed at three time points during the study: baseline (pre-randomisation), post-intervention (~ 6 weeks from the intervention beginning), and at a 3-month post-intervention follow-up. These methods are based on the RELATE trial protocol (version 4; 3 February 2021).

### Participants

#### Inclusion criteria

Aged 10 years, 0 months to 17 years, and 11 monthsClinically elevated PTSS at the initial screening stage, defined by scoring 17 or above on the Child Revised Impact of Events Scale (CRIES-8)In any type of care placement (including foster, kinship, residential or semi-independent care), with the exception of living with a biological parentAccess to appropriate technology and a private space to engage in the online sessions

#### Exclusion criteria

Severe psychosisCurrent active serious suicidal ideationsModerate to severe learning disability, which excludes the young person from accessing mainstream schoolingCurrently receiving direct trauma-focused therapeutic mental health support from any service

The exclusion criteria are primarily assessed through discussion with the young person’s social worker. In addition, if the baseline assessment indicates that the young person may meet the exclusion criteria, the social worker will be further consulted, and safeguarding and referral procedures followed as needed.

#### Sample size

A power calculation to determine sample size is not appropriate for a feasibility trial. Based on previous feasibility trials and guidelines [27], a sample size of 50 (25 per arm) is considered adequate to allow for the assessment of feasibility, including the monitoring of any adverse experiences or outcomes, as well as questions around uptake and retention rates for the intervention and CAU arms.

#### Recruitment, consent, assessments and randomisation

Participants will be recruited from the children’s social care recruitment site. Social workers (or an appropriate adult) will complete the CRIES-8 with the young person (see the ‘Measures’ section) and where they score 17 or above (the cut-off score found to maximise the probability of detecting clinically elevated PTSS whilst minimising the possibility of false positives [24];), and meet the remaining inclusion/exclusion criteria, they will be eligible for the trial.

The trial will be introduced to social work teams via attendance at team meetings and site professional development days, as well as via information sheets. Social workers, on behalf of the local authority in whose care the child is placed, will provide informed consent for eligible young people on their caseload. In some cases (e.g. based on care orders), biological parents will also be required to provide informed consent, which will be managed on a case-by-case basis with the support of the appropriate social worker. In these cases, both the social worker and parent must provide informed consent, and if there is a disagreement, the young person will be unable to take part (unless they are able to provide their own informed consent). Following this, the research team will contact the young person’s carer or keyworker (if in a residential care home) to provide them and the young person with information about the study, including audience-appropriate information sheets. Fully informed assent (or consent, where more appropriate) is required from young people who wish to participate, whilst carers and keyworkers will provide informed consent for their own participation. For young people in residential care, the keyworker will be considered the caregiver and invited to participate in the carer sessions. Young people will still be able to participate if their caregiver declines, but not vice versa. Where there are concerns about the young person’s comprehension of the study information, the researcher will ask the young person to give a verbal summary of what taking part will involve, in their own words. Informed consent and assent procedures include covering what the trial involves, that consenting does not guarantee that the young person will access the new intervention, confidentiality and the limits of this (i.e. for safeguarding), the use of audio recording, and the voluntary nature of the project (including that declining will not influence the care or support they receive). Young people who decline to participate will still receive care-as-usual from their social worker, which may include a referral to a mental health service.

Following informed assent or consent, the young person and the carer will complete the baseline assessments (see the ‘Measures’ section). Assessments at each time point can be completed over the phone or video, or in some cases, in person at the young person’s foster or care home, depending on the preference of the young person or carer (and following current Public Health England and University guidance relating to COVID-19). The questionnaires can be completed on paper or online (via a Qualtrics link to the questionnaire pack), whilst the diagnostic interview can be completed virtually, over the phone or in person. Participating young people can complete the self-report questionnaire pack independently or supported by the carer, but if needed (e.g. for younger participants), the researcher can also support the young person to complete the questionnaire pack. This is explored on a case-by-case basis. At the follow-up assessments, if a young person declines the qualitative and diagnostic interview, the questionnaire pack can still be completed online via Qualtrics.

Following the baseline assessment, participants will be randomly allocated to TRT or CAU, in a 1:1 ratio by an independent statistician using a computer-generated allocation sequence. Any young people entering into the trial who live in the same household will be randomised together. Randomisation will be stratified by age group (< 14 years or ≥ 14 years), and if children in the household are in different age groups, the age group of the household will be dictated by the mean age of the children. If randomised to the TRT condition, each child will be offered participation in the next age-appropriate group. The outcome of the randomisation will be shared with participants within 48 h.

For participants in the TRT arm, all baseline assessments will be carried out no more than 1 month prior to the first group session. In circumstances where the first session is more than 1 month after the baseline assessments, the young person and carer will be asked to complete the battery of assessments again before the group commences. See Fig. 1 for SPIRIT figure, which outlines key phases of the trial.

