#### Primary quantitative clinical outcome

##### Child and adolescent trauma screen (CATS [26];)

The primary outcome measure (administered at each assessment point) will be the young person self-report CATS, which has two parts. The first part is a 15-item trauma history checklist, where the young person marks ‘yes’ or ‘no’ to a list of criterion A trauma exposures. The second part is a 20-item DSM-5 PTSD symptom scale, with symptoms rated from 0 (*never*) to 3 (*almost always*)*.* Whilst the primary outcome is symptom change on the self-report CATS, carer report will also be collected as part of the feasibility study and change in symptoms based on carer report, reported as secondary analysis.

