##### Additional secondary clinical outcomes

Questionnaire measures assessing functioning and relationships will also be carried out at each time point, including the following:The Inventory of Parent and Peer Attachment - parent scale (IPPA [3];). The IPPA is a validated young person self-report questionnaire which assesses the quality of relationships between a young person and their friends and caregiver. In the current study, only the scale addressing the young person’s views on the caregiver relationship will be assessed, and the questionnaire has been adapted to use the wording ‘carer’ rather than ‘parent’. The IPPA - parent scale consists of 28 items which measure three subscales: trust, communication and anger and alienation, with items rated on a 1 (*almost never or never*) to 5 (*almost always or always*) scale. This measure will be completed by young people only.The Parent Trauma Response Questionnaire (PTRQ [33];). The PTRQ is a measure of parental appraisals and support style following a child’s experience of trauma. In the current study, we will use the PTRQ support style subscale, with wording amended to reflect carers, rather than parents. The support style subscale consists of 10 items which are rated on a scale from 0 (*not at all*) to 3 (*a lot*) and measures avoidant support style (e.g. *discouraging conversation about potentially traumatic experiences*) and approach support style (e.g. *allowing the young person to talk openly about their experiences*). This measure will be completed by carers only.The Child Health Utility 9D (CHU-9D [29];). The CHU-9D is a self-report measure of health-related quality of life which comprised 9 dimensions (*worried, sad, pain, tired, annoyed, schoolwork, sleep, daily routine* and *ability to join in with activities*). Each dimension is rated on 5 levels indicating increasing levels of severity, e.g. 1 (*I do not feel worried today*) to 5 (*I feel very worried today*). This measure will be completed by young people only.

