##### Qualitative measures

Several important feasibility and acceptability questions, for the overall protocol and intervention (see the ‘Aims’ section), will also be assessed via a series of qualitative focus groups and semi-structured 1:1 interviews, completed post-intervention with participants (young people and carers) and service providers (social workers and intervention facilitators).

All young people and carers who were randomised to the intervention arm, including those who withdrew at any point, will be invited to participate in separate 1:1 semi-structured interviews over phone/video. Interviews will focus on how the young person and carer found the intervention (including the online delivery format), whether there were specific components that did or did not work as well, how the carer found supporting the young person over the course of the programme, and general feedback on protocol procedures. To further explore the acceptability of the protocol, at least five participants from the CAU comparison arm will also be invited to participate in short qualitative interviews (over the telephone or by post), to ascertain their views of the recruitment procedures and CAU arm. Reasons for declining to participate will be routinely collected at all stages of the study.

For service -providers, two focus groups will be run, one within social care and one within the specialist CAMHS team. These will focus on experiences of the study protocol (including the online delivery format of the intervention), what did and did not work at different stages, and perceived barriers and how (and/or if) they overcame these.

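### The carer may help complete the young-person pack that contains the scale rating that same carer, which puts the IPPA (and, less strongly, the CATS) at risk of biased answers

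*Protocol article*

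**What the plan says.** Under Recruitment, consent, assessments and randomisation, the protocol article says "Participating young people can complete the self-report questionnaire pack independently or supported by the carer". Researcher help is a further option where needed, for example for younger participants: "the researcher can also support the young person to complete the questionnaire pack". The choice between these is left open: "This is explored on a case-by-case basis". No scale is taken out of carer support, and the rule is not limited to one visit or one arm.

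Under Additional secondary clinical outcomes, the IPPA is given at every time point and completed by young people only. Of this instrument, "only the scale addressing the young person’s views on the caregiver relationship will be assessed", with the wording changed from parent to carer. It has 28 items scored 1 to 5, in three subscales: trust, communication, and anger and alienation.

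The self-report CATS is also given at each assessment. "The first part is a 15-item trauma history checklist", covering criterion A exposures. The second part is the 20-item symptom scale, and change in symptoms is the primary clinical outcome.

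**The concern.** A young person who depends on a placement may be asked how far they trust the carer, or feel angry with or alienated from them, while that carer helps with the form. Self-report on such items relies on the rated person not seeing the answers. If some answers are softened, IPPA scores shift towards a good relationship, by an amount that depends on who was helped and at which visit.

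In this trial the data serve three purposes: descriptive summaries by arm, the check for ceiling and floor effects (Quantitative data), and the selection of secondary measures for the definitive trial (aim 1(d)). Softened answers could make the IPPA appear to sit near its ceiling, or to be insensitive, because of how it was collected.

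For the CATS the worry is milder. A young person may hold back on exposures or symptoms beside a carer, and a carer who knows the allocation may colour symptom answers after randomisation.

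**Working it through.** The plan gives no figure on this point, so the check is a reading of sections side by side, followed by an illustration of scale.

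**Reading**

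1. *Who may help.* Carer support is expressly permitted and researcher help is available. The choice is made case by case.
2. *What the pack holds.* The article does not itemise it. The IPPA and the self-report CATS are both young-person questionnaires given at each assessment, so both belong to it on a natural reading.
3. *Who is rated.* The IPPA asks about the carer. Under the recruitment section a keyworker counts as the caregiver in residential care. The helper and the person rated will therefore often be the same, although with two carers in a home they need not be.
4. *Safeguard.* The article states none for these scales: no private completion, and no record of who helped.
5. *Blinding.* The Blinding section covers the researcher who delivers post-intervention assessments. Carers in the TRT arm are invited to two carer sessions, so they know the allocation.
6. *Other sources for exposure.* Social workers report the severity of pre-care maltreatment (Descriptive statistics). The CPSS-I interview, with young people only, also takes criterion A history. Neither is complete: the first stops at entry to care, and the second can be declined at follow-up while the pack is still returned. The IPPA has no second source.

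**Illustration of scale (assumptions, not findings)**

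From the protocol: 28 items scored 1 to 5. If all items are aligned and summed, which the article does not state, the span is 28 × 1 = 28 to 28 × 5 = 140, a width of 112.

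Assumed: carer presence lifts each helped form by 0.2 to 0.4 points per item, and 20% to 60% of an arm is helped.

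Shift in arm mean = 28 × share helped × lift per item:
- low: 28 × 0.2 × 0.2 = 1.1 points
- high: 28 × 0.6 × 0.4 = 6.7 points

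If help were also 20 percentage points more common in one arm (assumed), the spurious difference would be 28 × 0.2 × 0.2 = 1.1 to 28 × 0.2 × 0.4 = 2.2 points.

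For comparison, with an assumed SD of 15 to 20 and all 25 per arm followed up, the 95% confidence half-width for a difference is 1.96 × SD × √(2/25). This gives 1.96 × 15 × 0.283 = 8.3 to 1.96 × 20 × 0.283 = 11.1 points. On these assumptions a difference in help between arms would be hidden within the sampling error.

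**The case against.** The strongest reply is that support is undefined. It may mean opening the link or reading a word aloud, independent completion is the first option named, and the mode is chosen case by case. That stands against any claim that answers are biased whenever a carer helps. A reader might infer this, but the document shows neither the presence nor the size of a bias.

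Second, the CATS exposure list is not an outcome. It is a general trauma history list and should not be read as a maltreatment checklist. Living with a biological parent is excluded, although kinship care is eligible ("In any type of care placement (including foster, kinship, residential or semi-independent care"), and exposure has the other sources set out above. This stands, and it makes the checklist the weaker part of the point.

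Third, a reader might infer that help becomes more common in the TRT arm because carers there attend sessions. Nothing in the article links those sessions to help with forms, so this is only a possibility.

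Fourth, a reader might see a contradiction with the qualitative interviews, where young people and carers "will be invited to participate in separate 1:1 semi-structured interviews over phone/video". There is none: those interviews collect each party's own experience of the intervention.

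Fifth, withdrawing carer help could lower completion, which is itself a primary feasibility outcome. This stands for the CATS, and is why carer help should not be barred there.

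Finally, the article condenses a fuller protocol, and privacy instructions or a field for who helped may sit in that document. This may answer the recording part. It does not answer the main part, because the article states a permission that covers every scale.

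**Conclusion.** The point holds as a risk of bias created by a stated rule. It is clearest for the IPPA, where the helper may be the person rated, and this applies at baseline and in both arms. It is weaker for the CATS, where the route that matters most is an unblinded carer helping with the primary symptom scale after randomisation.

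The size is unknown. The illustrative arm shifts of 1.1 to 6.7 points on a 112-point span rest wholly on assumed lifts and shares, and show only that the effect could range from trivial to noticeable. The conclusion also rests on the natural reading that both scales are in the pack.

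Severity is minor. The IPPA is an additional secondary outcome in a 50-person feasibility trial with descriptive analysis. The main consequence is for judging the measure before the definitive trial.

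**What to change.** In the recruitment and assessment section:

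- State that the IPPA is completed by the young person alone or with researcher help, and not with the carer.
- For the CATS, offer private or researcher-supported completion first, without ruling out carer help.
- Record for each pack and visit who helped: none, researcher or carer.
- Show IPPA and CATS results by who helped, or without carer-helped forms, as a sensitivity display. Helped participants may differ from the rest (younger, for instance), so the display is descriptive and does not correct for bias.

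The Trial status section says recruitment has begun. For packs already returned, the helper can be recorded only where it was noted. Otherwise the gap should be reported as a limitation.

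The cost is a sentence or two in the protocol and assessor instructions, a tick-box per visit, some extra researcher time, and possibly a few more missing IPPA forms. Packs completed remotely cannot be fully policed, so the recorded mode of help will be approximate.
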